### Statistical methods

We will compare the outcome variables (SDS, SAS, MAAS, Quality of Life Index, and MMAS) between the two groups using the χ^2^ test for categorical variables and Student t or Wilcoxon tests for continuous variables. Analysis of covariance (ANCOVA) will be conducted to assess whether MBSR is related to changes between baseline and after 8 weeks of intervention in relation to psychological status, QOL, and compliance behaviors.We will use a structural equation model [45] to examine the intervening role of mindfulness enhancement on improving mental health, QOL, and compliance with medical treatment. Mediation analysis, as implemented in MPlus 7.11, will be used to analyze the causal pathway from MBSR intervention to health outcomes through mindfulness enhancement.We will use a random-effects repeated measures analysis [46] to examine the impact of MBSR intervention on health outcomes, compliance behavior, adjusting for confounding variables (age, education, household income, occupation, previous cancer history, and household registration status: Shanghai vs. non-Shanghai). The repeated measure analysis approach accounts for the same individual’s different outcome measures across different points in time without assuming either linear or curvilinear growth pattern. Cronbach alpha’s will be computed to determine the internal consistency of our outcome measures. Using this approach (as implemented by the PROC MIXED and PROC GLIMMIX modules in SAS 9.0), we have published an article analyzing a famous randomized controlled trial of lung cancer screening, which shows a behavioral differential between the two trial arms [47].

The relationship between methods used for each hypothesis is shown in Table 1.

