### Primary hypotheses

Participants in MBSR would show improvements in mental health, QOL, and medication treatment compliance, relative to control subjects. We predict that MBSR would help reduce psychological distress and increase patients’ ability to monitor negative cognitions and thereby decrease stress.The levels of mindfulness would increase over the course of the 8-week MBSR program, serving as a mediator to positive changes in mental health, QOL, and medication treatment compliance.

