### Sample size

Based upon an MBSR study among BC survivors where the intervention group had significantly better aggregated physical health outcome as measured by SF-36 (50.3 among MBSR subjects vs. 46.9 among the control group) [44], we used STATA 12.0’s power calculator to find that our two-group, three-follow-up design needs 195 participants for each of the two groups, i.e., 390 subjects in total. Assuming an attrition rate of 10 % (attrition rate here means the percent of people who drop out from the study due to moving away, death, etc.), we concluded that we need to recruit a sample of 429 BC survivors at baseline.

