## Discussion

The largest threat to our study’s internal validity is the possible “contamination effect” (or spillover effect) between the two trial arms. As our participants will be recruited from 10 low-income communities from two of Shanghai’s poorer districts, it is possible that some of these participants know each other and may hold discussions regarding the MBSR treatment. The contamination effect could compromise measurable differences between the two trial arms and bias the intervention result toward the null hypothesis. However, as MBSR takes a substantial amount of exercise to achieve measurable results in mental health, it is unlikely that contamination alone could diminish the difference between those who attend the class and those who only hear about the practice. Plus, we will communicate to the waitlist control group in written materials to make sure that they start MBSR practice only when they receive the intervention.

**Table 1 Tab1:** Summary of methods used for each hypothesis

Objective (main study)	Hypothesis	Method
Objective 1	Primary Hypothesis 1: Improvement in mental health, quality of life, and medication treatment compliance in mindfulness-based stress reduction (MBSR) group	Method 1: Bivariate analyses and ANCOVA
	Primary Hypothesis 2: Relation between MBSR and improvement	Method 2: Mediation analysis in structural equation modeling
Objective 2	Secondary Hypothesis: Long-term improvement of MBSR	Method 3: Repeated measures analysis
Objectives 3 and 4	N.A.	Expert consultation

There is also the possible threat to internal validity through high attrition among participants. Attending an 8-week course is not a trivial matter for young working women, and thus it is possible that those who do not experience an immediate gain in mental health are more likely to quit. This possible pattern of selective attrition could lead to overestimation of intervention impact, as most of those who stay until the end of the intervention are more likely to experience MBSR benefits. We believe, however, that our financial incentive for participants should be sufficient for most BC survivors to complete the course, so long as we appropriately program the timing of our financial incentive (e.g., payment will be given out at each session, instead of being given out in a lump sum at the beginning).

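### Primary Hypothesis 1 spans four scales and two methods, with no primary scale, deciding test or success rule named

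*Protocol article*

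**What the plan says.** All references are to the protocol article.

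- **Primary hypotheses.** The first reads: "Participants in MBSR would show improvements in mental health, QOL, and medication treatment compliance, relative to control subjects". It names three domains and no scale. The second gives mindfulness a different role, "serving as a mediator to positive changes in mental health, QOL, and medication treatment compliance".
- **Statistical methods, unadjusted tests.** "We will compare the outcome variables (SDS, SAS, MAAS, Quality of Life Index, and MMAS) between the two groups". These comparisons are unadjusted: chi-square where the measure is categorical, and a t or Wilcoxon test where it is continuous. No time point is given for them.
- **Statistical methods, ANCOVA.** The sentence that follows reads: "Analysis of covariance (ANCOVA) will be conducted to assess whether MBSR is related to changes between baseline and after 8 weeks of intervention". This fixes the time point, but its outcomes are given as three domains (psychological state, quality of life and compliance), not as named scales.
- **Table 1 (Discussion).** Primary Hypothesis 1 is matched to "Method 1: Bivariate analyses and ANCOVA", with neither ranked first. Mediation analysis goes to Primary Hypothesis 2, and repeated measures analysis to the secondary hypothesis.
- **Sample size.** The calculation rests on an SF-36 physical health score, "50.3 among MBSR subjects vs. 46.9 among the control group". SF-36 is not among the outcome measures listed in the article.

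**The concern.** Naming the primary outcome and the analysis that decides it is core protocol content. Here one primary hypothesis is given several scales of equal standing and two methods of equal standing. The unadjusted test and the ANCOVA on one scale can disagree, and nothing says which prevails. The sample size section does not settle the matter, because its score is not an outcome of this trial.

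Two smaller points widen the choice. MMAS is described both as a 0 to 8 score and as three adherence categories, so either a continuous or a categorical test could be applied. MAAS is listed among the outcome variables although the hypotheses make it the mediator, which blurs the set of scales that Hypothesis 1 is judged on.

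What is at stake is the headline claim. Without a rule, the reading of success can be chosen after the results are seen, and the error rate and power depend heavily on that reading.

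**Working it through.** **Inputs from the article.** Five listed scales; four once MAAS is set aside as mediator. Two methods for Primary Hypothesis 1. 195 participants per group.

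**Assumptions (the article gives no figure).** Two-sided 5% per test; correlation between scales 0 to 0.7; correlation between baseline and follow-up 0.3 to 0.7; both tests made at 8 weeks on each of the four scales; 80% or 90% power behind the 195.

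**The plan's own figure.** The 195 cannot be reproduced, because SD, alpha, power and the repeated-measures correlation are not stated. Read as a simple two-group comparison of the difference 50.3 − 46.9 = 3.4, the implied SD at 80% power is 3.4 × √(195/2) / (1.960 + 0.842) = 11.98. At 90% power it is 10.36.

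**Step 1: any-scale rule, one test per scale, independent scales.**
- Four scales: 1 − 0.95⁴ = 0.185.
- Five, if MAAS were counted: 1 − 0.95⁵ = 0.226.

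**Step 2: any-scale rule, correlated scales, both methods.** Simulation under no effect on any scale, 400,000 draws, large-sample z tests. With baseline difference B, independent residual E and baseline-to-follow-up correlation r, the unadjusted statistic is rB + √(1 − r²)E and the ANCOVA statistic is E. The two tests on one scale are therefore correlated √(1 − r²). Results for four scales, in per cent:

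| Correlation between scales | One test per scale | Either test, r = 0.3 | Either test, r = 0.5 | Either test, r = 0.7 | Either test, in favour of MBSR (r = 0.3 to 0.7) |
|---|---|---|---|---|---|
| 0 | 18.5 | 23.3 | 26.2 | 29.3 | 12.2 to 15.6 |
| 0.3 | 17.4 | 21.8 | 24.6 | 27.4 | 11.0 to 13.8 |
| 0.5 | 15.6 | 19.5 | 22.0 | 24.6 | 9.8 to 12.4 |
| 0.7 | 13.0 | 16.3 | 18.5 | 20.6 | 8.2 to 10.3 |

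With both methods the range is about 16% to 29%, or about 8% to 16% in favour of MBSR. Counting MAAS as a fifth scale would give about 18% to 35%.

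**Step 3: all-scales rule.** Requiring all four unadjusted tests to be significant in favour of MBSR gives a simulated error of at most 0.3% when no scale has an effect. Power suffers instead. With 80% on each scale, joint power is 0.8⁴ = 0.41 if the scales are independent, and cannot exceed 0.80 however strongly they are correlated.

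**Step 4: cost of Holm across four scales.** The first step uses 0.05/4 = 0.0125, critical value 2.498. A test with 80% power at 0.05 has expected z of 1.960 + 0.842 = 2.802. Its power at the first step is Φ(2.802 − 2.498) = Φ(0.304) = 0.62. Starting from 90% power, Φ(3.242 − 2.498) = Φ(0.744) = 0.77.

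**The case against.** The best defence has four parts.

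1. **A multiplicity procedure may sit elsewhere.** The article condenses a fuller protocol and no analysis plan is shown. This stands: a reader might infer that the trial has no error control, but the absence of an adjustment method from the article does not establish that. It does not answer the main point, because the article itself gives one primary hypothesis two unranked methods and several unranked scales.
2. **The inflation depends on a success rule that the article never states.** The hypothesis joins its domains with *and*, and an all-scales reading has a very low error. This also stands. The any-scale figures show what one permitted reading would cost; they do not describe the plan. That both readings remain open is the defect.
3. **The hypotheses already separate MAAS.** A reader might infer that a rise in mindfulness alone could be declared a success. The wording of Hypothesis 1 does not support that, and a between-arm comparison of MAAS is a natural step towards Hypothesis 2. What remains is a loose label in Statistical methods.
4. **Unadjusted comparisons beside ANCOVA are common practice.** Agreed, provided that they are descriptive. Table 1 does not make them so.

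A reader might also count ten p-values, five scales by two methods. The text does not say this: ANCOVA is named for three domains, not for each of five scales.

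**Conclusion.** The concern holds in this form: for Primary Hypothesis 1 the article names no primary scale, no deciding test and no rule for success, and the sample size does not supply one. It should be settled before enrolment.

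The size depends on the reading. Under an any-scale rule at an assumed 5% per test, the error is roughly three to six times nominal when both methods are allowed (16% to 29%). About half of that would be in favour of MBSR. Under an all-scales rule, the problem is lost power. It would go too far to call a chance success likely: every figure for the four scales is below 30%, and those in favour of MBSR are below 16%. The correlations, the 5% level and the use of ANCOVA on each of the four scales are assumptions. The lack of a named primary outcome and deciding analysis does not depend on them.

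**What to change.** - Make the baseline-adjusted ANCOVA at 8 weeks the sole deciding analysis for Primary Hypothesis 1. It is already planned and already tied to that time point. Label the t, Wilcoxon and χ² results as descriptive.
- Then choose one of two routes. Either name one of SDS, SAS, Quality of Life Index or MMAS as primary (the sponsor's choice) and test the other three after it in a stated fixed sequence, or apply Holm across the four at two-sided 5%.
- Keep MAAS as the mediator under Primary Hypothesis 2, and remove it from the list of outcomes on which efficacy is judged.
- Restate the sample size for the chosen outcome, giving its difference, SD, alpha and power.

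**Cost.** The wording takes a few sentences and a correction to Table 1. At the time of writing the trial had not begun, so no data would have been seen. The statistical cost is a stricter threshold. Under Holm, if 195 per group was set for 80% power at 0.05, power at the first step is about 62% per scale (about 77% if it was set for 90%). Naming one primary scale avoids that loss for that scale, but later scales can be claimed only if those before them succeed. Redoing the power calculation may change the recruitment target.

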### Secondary hypotheses

MBSR would be an intervention modal with a long-term effect. We predict that at 1-year follow-up, the MBSR group would still show improvements in mental health, QOL, and medication treatment compliance, compared with its baseline levels.

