#### Implementation

Following completion of their hospital treatment, BC survivors return home. As part of the newly launched cancer registry system, each community health service center (CHSC) in Shanghai collects BC survivors’ detail information in order to ensure follow-up and to analyze mortality and morbidity rates. Based on the patient lists from CHSC, we will contact these BC survivors directly to recruit potential participants. All participants who are willing to attend this trial will be requested to submit a signed informed consent. After that, all participants who provide an informed consent will then complete a baseline questionnaire for psychometric assessment (Time 0), with the help from investigators. Information about demographic background and health status will also be collected and later verified by a review of hospital charts.

The immediate intervention group will start the program within 2 weeks of randomization. Two certified MBSR psychotherapists will be hired to implement a standard MBSR intervention. Members of the research team will attend each MBSR session to ensure that intervention standards are met.

All subjects will be reassessed after the intervention group completes half of the program (4 weeks into the intervention, Time 1), 8 weeks later (Time 2), and at 6 (Time 3) and 12 months (Time 4) from the beginning of the intervention. Participants in the control group will be given the opportunity to complete the MBSR program after 6 months follow-up. Eight investigators will be in charge of these follow-ups by telephone.

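### The repeated measures model adjusts for six background variables but makes no stated, efficient use of the baseline outcome, so between-arm contrasts after 8 weeks may lose precision

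*Protocol article*

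**What the plan says.** The Statistical methods section of the Protocol article sets out three strands that bear on this point.

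- Group comparisons of the outcomes by "Student t or Wilcoxon tests for continuous variables", followed by an ANCOVA: "Analysis of covariance (ANCOVA) will be conducted to assess whether MBSR is related to changes between baseline and after 8 weeks of intervention". The covariates of the ANCOVA are not named. Table 1 gives both to primary hypothesis 1.
- A mixed model: "We will use a random-effects repeated measures analysis [46] to examine the impact of MBSR intervention on health outcomes, compliance behavior", with the adjustment set "adjusting for confounding variables (age, education, household income, occupation, previous cancer history, and household registration status: Shanghai vs. non-Shanghai". The section adds that this approach "accounts for the same individual’s different outcome measures across different points in time without assuming either linear or curvilinear growth pattern".
- Table 1 assigns that model to the long-term question: "Secondary Hypothesis: Long-term improvement of MBSR Method 3: Repeated measures analysis". Under Secondary hypotheses the prediction is that at 1 year "the MBSR group would still show improvements in mental health, QOL, and medication treatment compliance, compared with its baseline levels".

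Baseline scores will exist for everyone. The Implementation section says that consenting participants "will then complete a baseline questionnaire for psychometric assessment (Time 0". Reassessment follows at 4 weeks, 8 weeks, 6 months and 12 months (Time 1 to Time 4). The waitlist arm is offered the programme after the 6-month follow-up.

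**The concern.** The article names an adjustment set for the mixed model, and the variable one would expect to predict follow-up scores best, the same score at Time 0, is not in it. If Time 0 is meant to be a response instead, an ordinary arm-by-visit model leaves the arm means free at Time 0. The between-arm contrast then becomes a comparison of changes, which is less efficient than adjusting for baseline.

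The contrast most exposed is the one at 6 months, the last before the waitlist arm may cross over. The ANCOVA stops at 8 weeks. A between-arm result at 6 months must therefore come from the mixed model or from an unadjusted test. Wider standard errors there would be a cost in power that the data already collected could avoid.

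**Working it through.** **Inputs from the article.** Two arms of 195 (Sample size section), after allowance for attrition; Time 0 on all; five assessments.

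**Inputs assumed.** The baseline to follow-up correlation r is not given, so 0.3 to 0.7 is shown. It should be read as the correlation left after the six background variables. Also assumed: equal variances and equal correlations across visits, complete data, continuous scores.

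**The plan's own figure.** The 195 per arm cannot be reproduced, because the standard deviation, alpha, power and correlation are not stated. For the cited difference of 50.3 − 46.9 = 3.4 in a simple two-sided 5% comparison, 195 per arm corresponds to a standard deviation of 3.4/(1.960 + 0.842) × √(195/2) = 12.0 at 80% power, or 10.4 at 90%. Below, 195 serves only as the arm size.

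**Codings that fit the text.** For the between-arm contrast at one follow-up visit, with outcome SD σ and n per arm:

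- A. Follow-up visits only: variance (2σ²/n) × 1
- B. Time 0 as a response, arm means free: (2σ²/n) × 2(1 − r)
- C. Time 0 as a response, arm means equal at Time 0: (2σ²/n) × (1 − r²). Entering Time 0 as a covariate gives the same variance.

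With n = 195, A has standard error √(2/195) = 0.101σ.

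| r | SE, A | SE, B | SE, C | Variance of C below A | Variance of C below B |
|---|---|---|---|---|---|
| 0.3 | 0.101 | 0.120 | 0.097 | 9% | 35% |
| 0.5 | 0.101 | 0.101 | 0.088 | 25% | 25% |
| 0.6 | 0.101 | 0.091 | 0.081 | 36% | 20% |
| 0.7 | 0.101 | 0.078 | 0.072 | 49% | 15% |

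The reduction against A is r². Against B it is 1 − (1 − r²)/[2(1 − r)] = (1 − r)/2. Generalised least squares standard errors for a five-visit model with 195 per arm agree with these formulas.

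**In terms of power.** Suppose, only as an anchor, that coding A had 80% power at two-sided 5%. Power under C is then Φ(2.802/√(1 − r²) − 1.960) = 84, 90, 94 and 98% at r = 0.3, 0.5, 0.6 and 0.7. Under B, with √(2(1 − r)) as the divisor, it is 66, 80, 88 and 95%.

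**Which coding does the article mean?** The secondary hypothesis compares the MBSR arm at 1 year with its own baseline, so Time 0 probably belongs among the responses. That points to B or C rather than A. Nothing in Statistical methods states the constraint that separates C from B.

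**The case against.** The strongest reply has three parts. First, the primary 8-week analysis already uses baseline through the ANCOVA on change. Second, the mixed model is assigned to a within-arm comparison with baseline, which requires Time 0 as a response; the Time 0 score should then not also be a covariate, so its absence from the list would be correct. Third, the coding of Time 0 is a detail that an article may leave to a fuller document, and the list is not declared exhaustive.

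Much of this stands. A reader might infer that precision is lost on every outcome. The documents do not support that: the ANCOVA covers psychological status, quality of life and compliance at 8 weeks, and coding C, which the text does not rule out, loses nothing. A reader might also infer that alternating down a name-sorted list makes baseline imbalance worse and adjustment more urgent. The article gives no evidence that name order is related to baseline scores. The allocation method is a separate matter, which baseline adjustment does not resolve.

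What the reply does not remove is that the article states an adjustment set and describes the model as examining the effect of the intervention, which is a between-arm question. Two of the three codings that fit its words are inefficient. Having Time 0 as a response is not enough without the equal-means constraint. The unadjusted tests also sit beside the ANCOVA for primary hypothesis 1 with no statement of which one decides.

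**Conclusion.** The point holds in a limited and conditional form. As written, the mixed model does not secure efficient use of the baseline outcome, and the t and Wilcoxon tests do not use it at all. For one between-arm contrast, the avoidable variance is 9 to 49% of that of a follow-up-only model, rising with r from 0.3 to 0.7, or 35 to 15% of that of a model with free baseline means, falling with r. It is zero if the arm means are already meant to be equal at Time 0.

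These figures rest on an assumed correlation and on continuous scores. They do not carry over directly to medication adherence if it is analysed in categories. The consequence falls mainly on the 6-month comparison. It is a loss of power, not a bias in the planned analysis, and it is worth correcting because the remedy is so cheap.

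**What to change.** - In the mixed model, keep Time 0 to Time 4 as responses, with visit effects and arm-by-visit effects, and constrain the arm means to be equal at Time 0. Do not also enter the Time 0 score as a covariate. The six background variables can stay.
- Take the between-arm contrast at 6 months from this model. The same fit supplies the comparison of the MBSR arm at 12 months with baseline. A version with Time 0 as a covariate and only Time 1 to Time 3 as responses would not serve that comparison.
- Name the baseline score as the covariate of the ANCOVA and make it the 8-week test. Label the unadjusted t and Wilcoxon tests as descriptive.

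The cost is a few sentences in Statistical methods and no new data. The constraint presumes that allocation is unrelated to baseline scores and that Time 0 is completed before participants learn their arm. The order of steps under Implementation suggests the latter, and it should be stated.
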